# Healthy Mom Zone Adaptive Intervention With a Novel Control System and Digital Platform to Manage Gestational Weight Gain in Pregnant Women With Overweight or Obesity: Study Design and Protocol for a Randomized Controlled Trial

**DOI:** 10.2196/66637

**Published:** 2025-03-13

**Keywords:** pregnancy, gestational weight gain, physical activity, healthy eating, overweight, obesity, intervention

## Abstract

**Background:**

Regulating gestational weight gain (GWG) in pregnant women with overweight or obesity is difficult, particularly because of the narrow range of recommended GWG for optimal health outcomes. Given that many pregnant women show excessive GWG and considering the lack of a “gold standard” intervention to manage GWG, there is a timely need for effective and efficient approaches to regulate GWG. We have enhanced the Healthy Mom Zone (HMZ) 2.0 intervention with a novel digital platform, automated dosage changes, and personalized strategies to regulate GWG, and our pilot study demonstrated successful recruitment, compliance, and utility of our new control system and digital platform.

**Objective:**

The goal of this paper is to describe the study protocol for a randomized controlled optimization trial to examine the efficacy of the enhanced HMZ 2.0 intervention with the new automated control system and digital platform to regulate GWG and influence secondary maternal and infant outcomes while collecting implementation data to inform future scalability.

**Methods:**

This is an efficacy study using a randomized controlled trial design. HMZ 2.0 is a multidosage, theoretically based, and individually tailored adaptive intervention that is delivered through a novel digital platform with an automated link of participant data to a new model-based predictive control algorithm to predict GWG. Our new control system computes individual dosage changes and produces personalized physical activity (PA) and energy intake (EI) strategies to deliver just-in-time dosage change recommendations to regulate GWG. Participants are 144 pregnant women with overweight or obesity randomized to an intervention (n=72) or attention control (n=72) group, stratified by prepregnancy BMI (<29.9 vs ≥30 kg/m^2^), and they will participate from approximately 8 to 36 weeks of gestation. The sample size is based on GWG (primary outcome) and informed by our feasibility trial showing a 21% reduction in GWG in the intervention group compared to the control group, with 3% dropout. Secondary outcomes include PA, EI, sedentary and sleep behaviors, social cognitive determinants, adverse pregnancy and delivery outcomes, infant birth weight, and implementation outcomes. Analyses will include descriptive statistics, time series and fixed effects meta-analytic approaches, and mixed effects models.

**Results:**

Recruitment started in April 2024, and enrollment will continue through May 2027. The primary (GWG) and secondary (eg, maternal and infant health) outcome results will be analyzed, posted on ClinicalTrials.gov, and published after January 2028.

**Conclusions:**

Examining the efficacy of the novel HMZ 2.0 intervention in terms of GWG and secondary outcomes expands the boundaries of current GWG interventions and has high clinical and public health impact. There is excellent potential to further refine HMZ 2.0 to scale-up use of the novel digital platform by clinicians as an adjunct treatment in prenatal care to regulate GWG in all pregnant women.

**International Registered Report Identifier (IRRID):**

DERR1-10.2196/66637

## Introduction

### Background

High maternal prepregnancy BMI and high gestational weight gain (GWG) elevate the risks for poor pregnancy outcomes (eg, gestational diabetes and hypertension) and fetal outcomes (eg, large for gestational age birth weight) [1-6]. High BMI and GWG may also “program” the child’s metabolism for life [7,8] and increase the future risks for obesity and type 2 diabetes in both mothers and their offspring [1-6]. As such, managing GWG has high clinical and public health significance, and it can improve maternal health and impact the etiology of obesity or diabetes in offspring at a crucial time in the life cycle [1-6,8].

Guidelines from the Institutes of Medicine (IOM) [1] and National Academy of Medicine [2] recommend that the optimal total GWG should be based on a woman’s prepregnancy BMI category (ie, overweight: 6.8-11.3 kg; obese: 5.0-9.1 kg). However, evidence from a meta-analytic review including over 1 million pregnant women found that nearly 50% of women exceeded their recommended goals [9], and this was prevalent among those with normal weight as well as those with overweight or obesity. Furthermore, data from a meta-analysis of almost 200,000 women from 25 international cohort studies in the LifeCycle Project [6] showed the highest risk for adverse outcomes among women with both high BMI and high GWG. Given these concerns as well as the rapidly changing landscape of health care delivery since the COVID-19 pandemic, there is a critical and timely need for scalable approaches to effectively regulate GWG. One such strategy that may reach more pregnant women and reduce the burden on prenatal clinicians who monitor GWG is an automated approach that relies on a digital platform with remote delivery and passive remote data collection to monitor and effectively and efficiently regulate GWG.

### Prior Work

Our team’s prior work successfully constructed energy balance models to predict maternal GWG [10] and infant birth weight [11]. Expanding the work of Thomas et al [12], we built a novel dynamic mathematical model of energy balance and behavior to predict GWG [13,14]. It describes how physical activity (PA) and energy intake (EI) behaviors are influenced by social cognitive determinants (attitude, subjective norm, perceived control, intention, and self-regulation) [15-17] and depicts how components (ie, education, behavior coaching, goal setting, nutrition counseling, and engaging in PA and healthy eating activities) impact PA and EI social cognitive determinants and behaviors to regulate GWG. We also explored how the energy balance model could be extended to explain infant birth weight [11,18].

Prior research has shown that behavioral interventions can impact GWG [19-27] and more specifically that participants who received behavioral intervention components (eg, counseling, guided PA, and prescribed diet) had a lower mean GWG, decreased likelihood of exceeding GWG guidelines, and lower risk for adverse maternal and infant outcomes [20]. There was also evidence for a dose-response relationship whereby intensive interventions with more subject contact were associated with a stronger impact on GWG [20]. Moreover, the findings from qualitative and prospective cohort studies support an intensive approach to managing GWG in pregnant women with overweight or obesity because they may be more likely than women with underweight or normal weight to overestimate the amount of weight they should gain, underreport EI, and have low motivation to engage in PA on their own [28-41]. Taken together, there is ample evidence from the literature for an approach that considers the unique needs of pregnant women with overweight or obesity and personalizes intervention dosages to regulate GWG.

Many GWG interventions use a “one size fits all” approach and are not designed to consider individual variability in how women gain weight over the course of gestation. Our approach adapts personalized dosages for each woman in a way that gives more intensive treatment only to the women who need more assistance to regulate GWG. We piloted a proof-of-concept study [42] and feasibility-initial impact randomized trial [8,10,19,43-45] to examine the impact of the Healthy Mom Zone (HMZ) intervention on GWG. The social cognitive theory–based components [15-17] noted above were designed with the Multiphase Optimization Strategy [46] translational science framework [47-50], and control systems methodology [51-55], with the long-term goal to scale-up use by clinicians as an adjunct treatment to prenatal care in order to regulate GWG. This multiphase approach [46] builds an intervention in a principled manner whereby key constraints expected to impact scalability (eg, implementation feasibility and subject or staff burden) are considered from the start so that the end goal is an optimized (effective and efficient) and scalable intervention that delivers the best possible outcome [46]. Our translational science framework [47-50] guided by the Quality Implementation Framework [49] and Quality Implementation Tool [50] aligns with the paradigm shift in the literature to prospectively examine implementation markers (eg, subject acceptability, dosage exposure, and staff burden) from the start of an intervention to identify and resolve challenges during delivery that impact efficacy and scalability [49,50].

Our feasibility trial that randomized 31 pregnant women with overweight or obesity to the adaptive GWG intervention (delivered in person or remotely) or a control group over the course of pregnancy and used mobile health tools and online surveys to measure study outcomes showed high measurement compliance (85%), low burden (eg, average 1 min per day to complete measures), and low attrition (3%) [19]. The control system driven by decision rules and a woman’s observed GWG informed when to adapt dosages (GWG within goals [1,2], maintain dosage; GWG greater than goals, adapt dosage) [19]. Participants in the intervention group had a 21% lower mean GWG and were more likely to have GWG within goals than controls. Exploratory analyses showed promise for the HMZ intervention to impact secondary outcomes, including PA minutes, active kcal, EI kcal, and PA and EI social cognitive determinants. Furthermore, maternal nighttime awakenings were related to higher GWG [45], and maternal eating behaviors (uncontrolled eating or restraint) were related to GWG and infant birth weight [44].

Because our long-term goal is to deliver the best possible impact on GWG and maternal or infant outcomes and develop an approach that is scalable for future use in the real world, we used these feasibility findings to make refinements to the intervention content (eg, promoting healthy sleep or eating behaviors), delivery (all content available for remote delivery to ensure scalability), and decision process for evaluating and predicting GWG. More specifically, our initial control system was manually operated (ie, plotted each woman’s weight in individual participant files) and not particularly scalable. We thus improved this system by designing a new model-based control system with a hybrid model predictive control algorithm and our dynamic model of energy balance and behavior (Figure 1) [10,13,56]. This enables projections of within-person GWG over time (even when data are missing at the current time point) and has been found in past studies to yield robust personalized suggestions and accurate inferential results even with missingness [56-68]. We also built an architecture for a novel digital platform that makes it possible to deliver just-in-time recommendations directly to a subject in ways that target a broader array of outcomes and can reach more women. The platform provides a web-based interface equipped with secure user access control that automates the linkage of subject data collected with mHealth tools to the new model-based predictive control system that implements a Control Optimization Trial approach [10,51] consisting of semiphysical system identification and Hybrid Model Predictive Control. The platform displays graphical or numeric summaries of a woman’s past weight, behaviors (eg, PA, EI, and sleep), social cognitive determinants, and other factors; computes optimized dosage changes across multiple maternal variables; and produces a host of personalized PA or EI strategies to regulate GWG. This refined version of the intervention is denoted HMZ 2.0.

In order to activate recruitment, examine participant compliance with the measurement protocol, pilot test the HMZ 2.0 data transfer pipeline, examine intervention session delivery and user acceptability of the digital platform, and conduct simulations for controller-recommended dosage changes, we conducted a 28-day pilot study.

**Figure 1 figure1:**
[figure not shown]
Dynamic model of energy balance and behavior to predict gestational weight gain (GWG). The intervention components are education, counseling, goal-setting, self-monitoring, and physical activity (PA)/healthy eating (HE) active behavior strategies (eg, guided activity sessions and cooking demonstrations). The figure depicts the block diagram of the closed-loop control system framework for managing GWG in pregnant women with overweight or obesity and describes the influence of intervention components, baseline intervention dosage, and gestational age (GA) on GWG. The participant model consists of 2 behavioral models targeting PA and energy intake (EI) behaviors, respectively, and an energy balance model. Outputs from the behavioral models serve as inputs to the energy balance model, which calculates changes in GWG by assessing the difference between EI and energy expenditure. The hybrid model predictive controller (HMPC) uses filtered signals of set point and measured disturbances (baseline intervention dosage and GA). A Type-I filter is used to filter the baseline, represented by a binary signal that indicates the preintervention phase (0) or the intervention phase (1). In contrast, a Type-II filter is used to filter the set point and GA. The HMPC-based optimizer determines a sequence of control actions, referred to as PA and HE dosage augmentations. BS: baseline; IOM: Institutes of Medicine.

#### HMZ 2.0 Pilot Study Results

We recruited and enrolled 10 pregnant women (mean age: 32.1 years; mean gestational age at enrollment: 14 weeks). Participants completed the HMZ 2.0 preintervention measurement protocol lasting 7 to 9 days (depending on the day of enrollment), completed daily and weekly study measures over a 3-week period while also participating in three 60-minute weekly intervention sessions (content from the first 3 weeks of the HMZ 2.0 baseline intervention) delivered by a trained staff member through the HMZ 2.0 digital platform, and completed the postintervention measurement protocol (7-9 days) and a poststudy brief interview to understand user acceptability. The results of this pilot study are presented below.

We had 59 participant contacts, of which 31 (53%) were assessed for eligibility and 10 (32% of eligible participants) were enrolled in the pilot study. Successful recruitment of participants involved social media (30%), community-based flyers and handouts (eg, campus locations and local events such as farmer’s markets; 30%), word of mouth (20%), and clinic referrals (20%).

Participant compliance with the HMZ 2.0 measurement protocol was excellent, with compliance rates of 88% for the daily or weekly online surveys and MyFitnessPal app, 92% for using the Fitbit Aria Wi-Fi scale each day to assess weight, and 98% for wearing the Fitbit Charge 6 monitor each day to assess PA, sedentary behavior, and sleep behaviors. Moreover, the flow of data through the HMZ 2.0 pipeline was exceptional. Data transfer from devices and Research Electronic Data Capture (REDCap) to the digital platform was smooth, with <2% evidence of technical problems or glitches, and 100% of problems were resolved without issue.

A total of 30 intervention sessions (3 per participant) were delivered, of which 80% (24/30) were delivered with a hybrid approach (in person with the platform) and 20% (6/30) were delivered with a fully remote approach using Zoom and the platform. Attendance and compliance with the sessions were 100%. All the women (10/10, 100%) liked the utility of the HMZ 2.0 digital platform, and 90% (9/10) liked to see their real-time data and set weekly goals with trained study staff. In the poststudy brief interview, 1 woman commented that it was “nice to use [the platform] prior to sessions so I was able to come prepared and ask questions.” Another woman said, “The platform was easy to move from page to page.” A third woman noted, “We covered different topics during the sessions, so I liked being able to go back to the platform and look at the content again.” The participants also provided constructive feedback on the platform and suggested the following refinements: soften the color scheme on the website pages, include a page with session schedule and location information, and include a link to directly email the study staff to reduce the burden of looking through study materials for contact information. The platform was refined to address these concerns.

Simulations to illustrate the estimated model are presented in Figure 2, which shows the Control Optimization Trial framework for the recommended dosages within the system identification phase, adhering to the 2-week and 3-week delay. The first panel displays the participant’s weight in pounds (black solid line) and the setpoint (solid magenta line), which indicates the mean of the IOM guidelines (dashed red line) [1]. Different colors are used to represent the various intervention phases. The preintervention phase lasts for 7 to 9 days (9 days in this case), followed by a 2-week baseline period. During both the preintervention and baseline phases, no augmentations or dosages are administered. The first dosage is recommended after 2 weeks in the dosage 1 phase, starting on gestational day 126. The second dosage follows 2 weeks after dosage 1 in the dosage 2 phase. The second panel contains 2 subpanels: one for the manipulated variable augmentation PA and another for PA kcal. The last panel similarly includes subpanels for augmentation healthy eating and EI kcal. The simulation results show that the hybrid model predictive controller effectively manages the participant’s weight within the IOM bounds once the controller is activated. As illustrated, both in the system identification and controller phases, recommendations for PA or healthy eating dosages lead to reduced EI (healthy eating dosage recommended) or increased PA (PA dosage recommended), ultimately facilitating weight reduction through decreased EI and increased PA.

After the dosage 2 phase, the controller phase begins, during which the controller recommends further dosages based on predicted participant weight and the logic outlined in Figure 3, which illustrates the conceptual framework for the controller’s augmentation or dosage recommendations, operating similarly to a finite state machine. Each state is represented by 2 digits: the first digit denotes augmentation PA (PA dosage) and the second digit indicates augmentation EI (healthy eating dosage), and either the PA dosage or EI dosage is updated at any given time. The controller recommends dosages with a minimum user-specified delay of 2 weeks between all dosages, except between dosage 2 and dosage 3, where a 3-week delay is specified. Transitions between dosages are governed by an auxiliary signal *a_k_*. If *a_k_* equals 1, the controller can transition from the current dosage state to the next; otherwise, it remains in the current dosage state.

**Figure 2 figure2:**
[figure not shown]
Simulation illustrating the various stages of the control optimization trial implemented in the Healthy Mom Zone (HMZ) 2.0 intervention using an estimated model of an HMZ 1.0 representative participant. EI: energy intake; HE: healthy eating; HMPC: hybrid model predictive controller; IOM: Institutes of Medicine; PA: physical activity; RMSE: root mean square error.

**Figure 3 figure3:**
[figure not shown]
Dosage sequence pattern for the hybrid model predictive controller within the Healthy Mom Zone (HMZ) 2.0 intervention.

### Goal of This Study

The goal of this study is to describe the protocol for a randomized controlled optimization trial to examine the efficacy of the enhanced HMZ 2.0 intervention with the new automated control system and digital platform to regulate GWG and influence secondary maternal and infant outcomes while collecting implementation data to inform future scalability. Aim 1 is to examine the efficacy of the intervention in terms of GWG (primary outcome) and maternal PA and EI behaviors and social cognitive determinants on comparing intervention and control groups. It is hypothesized that the intervention group will (1) have lower pre- to postintervention GWG and be more likely than controls to achieve GWG within the guidelines [1,2], and (2) have higher PA kcal (and total kcal) and PA or EI determinants and lower EI kcal than controls. Aim 2a is to measure pre- to postintervention differences in secondary maternal sleep and eating behaviors. It is hypothesized that the intervention group will have fewer nighttime awakenings and less uncontrolled eating than controls. Aim 2b is to examine the impact of the intervention on birth weight and adverse pregnancy, labor, and delivery outcomes. It is hypothesized that the intervention group will show lower birth weight adjusted for gestational age and will have lower occurrences of adverse pregnancy, labor, and delivery outcomes than controls. Aim 3 is to examine the impact of implementation markers on intervention efficacy in terms of GWG and secondary outcomes. It is hypothesized that subject engagement, acceptability, dosage exposure, and staff burden or acceptability will moderate the effect of the intervention on study outcomes. This information will inform how to scale-up the HMZ 2.0 intervention for future use by prenatal clinicians.

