### Control Optimization Trial Procedures

Control systems methodology [51-54] in a novel Control Optimization Randomized Controlled Trial (RCT) [51] is used to test the efficacy of the enhanced HMZ 2.0 intervention with a novel digital platform and a new automated control system to regulate GWG and influence secondary outcomes. This idiographic approach uses individual dynamic models (integrating behavioral and energy balance models) informing how each woman responds to HMZ 2.0 to make personalized decisions about intensifying dosages to regulate GWG. We are not aware of any other studies using this unique strategy to regulate GWG. Women start the intervention with an “open-loop” experimentation phase and receive the HMZ 2.0 baseline intervention (dosages are not yet adapted during this time). Semiphysical models estimated using concepts from system identification [85,118-120] allow individual energy balance and behavior models to be built for each subject [51]. Model and dosage personalization is further enhanced by leveraging our team’s expertise in time-varying dynamic systems (systems that show changes in statistical properties over time) and multilevel models that integrate individual- and group-based dynamics and missing data issues [56-68]. Model components are measured with real-time data procedures to predict corresponding deviations from each woman’s target GWG range: overweight, 6.8-11.3 kg total and 0.23-0.32 kg/wk; obese, 5.0-9.1 kg total and 0.18-0.27 kg/wk [1,2]. Model estimation is used to confirm individual models and identify if certain constructs provide maximum impact for the control system. The goal of this open-loop phase is to arrive at a set of personalized dynamic models that capture the effects of dosage augmentations, gestational age, and the baseline intervention. Once the models are identified and the controller commissioned, models will not be updated, but the tuning parameters can be adjusted, if necessary. While there is no set threshold of data compliance for building individual models (models can be built with as little as 50% missing data handled with maximum likelihood estimation) [56-68], we will rely on strategies to achieve high compliance (90%; 10% missing data) similar to that in our feasibility study [19].

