
### Statistical Analysis

For study aims 1 and 2, time series methodology will be used on a subject basis (ie, cubic polynomial spline 3-lag auto-regressive models with maximum likelihood as the estimation method) followed by a fixed effects meta-analytic approach to combine information in order to compare the intervention group to the control group [141-143]. Mixed effects models will be used when the meta-analytic approach does not fit the data [56,62-65]. Potential confounding variables (eg, maternal age, parity, and income; infant sex; and adverse maternal-infant outcomes) [6,144] will be included in the models as covariates when appropriate. We will explore the extent to which prenatal sleep and eating behaviors impact postintervention GWG, PA, or EI and infant birth weight to inform modifications to the maternal energy balance and infant birth weight models. The intent-to-treat principle will be followed. Our statistical approach is robust if data are missing at random (multiple imputation will be considered if missing data are problematic) [145]. Hypothesis tests will invoke a 2-sided significance level of .05. Analyses for the synthesis of mHealth data and the predictive control system are informed by MATLAB toolkits and past experience [51,146,147]. Model personalization will use control-theory models, and requisite computations will be performed for optimal dosage changes [112,113,128,148-150]. For study aim 3, descriptive statistics will be used to examine the percentage and frequency for implementation markers. Formative methods will be used to organize, code, and rank order interview data [136,137]. Study findings will be used to further optimize HMZ 2.0 for effectiveness and scalability. Data will be collected and stored in REDCap [88]. Deidentified data will be exported from REDCap [88] to statistical packages. Subject confidentiality will be maintained with subject IDs. Data security is ensured with Penn State standard procedures.

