### Power Calculations

The primary outcome is GWG: absolute difference between the intervention and control groups for the mean change in GWG from the start to the end of the trial. From our feasibility study [19], we found that the difference between the intervention and control groups with respect to the absolute mean change in GWG from the start to the end of the trial was 1.9 kg (SD 4.9 kg), with an approximately 21% relative reduction for the intervention group compared to the control group. We compared the mean change in our feasibility trial [19] to that in several other GWG studies comparing intervention and control groups [29,151-154] and found that the intervention group gained on average 1.8 kg less than controls (range: 1.1-3.1 kg). The sample size of 144 randomized to the intervention (n=72) and control (n=72) groups in the proposed research is informed by our feasibility trial showing a mean difference of 1.9 kg (SD 4.9 kg), a 21% relative reduction in GWG in the intervention group compared to the control group, and a 3% dropout. Given our experience with the feasibility trial [19], the series of refinements that we performed following the feasibility trial (eg, adding content on sleep and eating behaviors given their effects on GWG; modifying all content for remote delivery given 100% compliance found for remote sessions in the feasibility trial; replacing the initial control system to make dosage change decisions with the new, automated, dynamic model-based predictive control system that outperformed the initial system for regulating GWG; and adding the novel HMZ 2.0 digital platform to adapt dosages), and the findings from our HMZ 2.0 pilot study (average weekly GWG over the 4-week study period: 0.3 kg, SD 0.4 kg; overall GWG from pre- to postintervention: 1.2 kg, SD 0.8 kg), we expect the HMZ 2.0 intervention to be more effective. We anticipate that our mean difference will be closer to what a recent study [155] found for the mean difference in GWG between the intervention and control groups (mean 3.6 kg, SD 5.7 kg). Conservatively, considering this larger SD of 5.7 kg and anticipating a larger dropout rate of 10%, the sample size of 144 yields 80% statistical power with a 2-sided significance level of .05 to detect an absolute difference of at least 2.9 kg in GWG between groups. Sample sizes for semistructured interviews are adequate to observe data saturation [136,137,141].

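### Aim 1 tests only the within-guideline share, which nets fewer women above the range against more below it and can stay flat at the powered effect; above and below should be compared by arm as well

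*Protocol article*

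**What the plan says.** Under Goal of This Study, hypothesis (1) of Aim 1 is that the intervention group will "have lower pre- to postintervention GWG and be more likely than controls to achieve GWG within the guidelines". No hypothesis concerns exceeding the range or falling below it.

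Control Optimization Trial Procedures gives the ranges as "overweight, 6.8-11.3 kg total and 0.23-0.32 kg/wk; obese, 5.0-9.1 kg total and 0.18-0.27 kg/wk", and Background gives the same totals. The Primary Outcome section gives other ranges: 14.1-22.7 kg (overweight) and 11.3-19.1 kg (obese).

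Power Calculations sizes the trial on mean gain only: "the sample size of 144 yields 80% statistical power" "to detect an absolute difference of at least 2.9 kg in GWG between groups", "considering this larger SD of 5.7 kg and anticipating a larger dropout rate of 10" per cent. It also cites the feasibility result: a difference of 1.9 kg, SD 4.9 kg, about a 21% reduction. No within-range rate or control mean is stated.

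The introduction frames the problem as excess: "nearly 50% of women exceeded their recommended goals" (Background), and earlier interventions are credited with a "decreased likelihood of exceeding GWG guidelines" (Prior Work).

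**The concern.** A two-sided band is a net measure. If an intervention lowers gain across the board, some women enter the band from above and others leave it at the bottom. When the band is narrower than one SD, the two flows can be nearly equal.

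A trial that achieves its powered effect could then report no difference in guideline adherence. That result would hide two things a reader needs: fewer women with excessive gain, which is the problem the introduction sets out, and more women with insufficient gain, which Safety Considerations treats as an adverse event.

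**Working it through.** **Inputs from the article.** Two-sided alpha .05; 72 per arm; 10% dropout, so 72 × 0.9 = 64.8 per arm; SD 5.7 kg (4.9 kg in the feasibility trial); effect 2.9 kg; ranges 6.8-11.3 and 5.0-9.1 kg.

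**Assumptions, not in the article.** Control mean 1.9 / 0.21 = 9.05 kg (back-calculated); normal distribution; equal SD in both arms; BMI groups 50:50; the same 2.9 kg shift for every woman.

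**1. The plan's own figure.** A two-sample t test with 64.8 per arm, difference 2.9 kg and SD 5.7 kg has 82.0% power. The difference detectable at 80% is 2.83 kg. The stated 80% for 2.9 kg is reproduced and slightly conservative.

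**2. Identity.** The three shares sum to 1, so change in within = −(change in above) − (change in below). This needs no model.

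**3. Width against spread.** The widths are 11.3 − 6.8 = 4.5 kg and 9.1 − 5.0 = 4.1 kg. A normal distribution centred on the band puts 2Φ(half-width / SD) − 1 inside. At SD 5.7 that is 2Φ(2.25/5.7) − 1 = 30.7% (overweight) and 2Φ(2.05/5.7) − 1 = 28.1% (obese). With that SD in both arms, no shift of the mean can do better.

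**4. Base case, SD 5.7.** Below = Φ((L − m)/SD); above = 1 − Φ((U − m)/SD); m = 9.05 (control) and 6.15 (intervention).

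| | Below | Within | Above |
|---|---|---|---|
| Overweight | 34.7 → 54.6% | 30.7 → 27.1% | 34.6 → 18.3% |
| Obese | 23.9 → 42.0% | 26.5 → 27.8% | 49.6 → 30.2% |
| 50:50 mix | 29.3 → 48.3% | 28.6 → 27.4% | 42.1 → 24.3% |
| Change, mix | +19.0 | −1.1 | −17.9 |

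Two-proportion power at 64.8 per arm is about 5% for within and 58% for above. At SD 4.9 the changes are +21.6, −1.7 and −19.9 points, with power about 5% for within and 69% for above. Moving the BMI mix from all obese to all overweight gives within changes of +1.3 to −3.6 points (SD 5.7) or +1.9 to −5.3 (SD 4.9).

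**5. Higher control mean, common 2.9 kg shift.**

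| Assumed control mean | Within, SD 5.7 | Within, SD 4.9 |
|---|---|---|
| 11 kg | +3.3 | +4.9 |
| 13 kg | +6.8 | +9.7 |
| 15 kg | +8.4 | +11.0 |

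Power for within stays below 40% throughout.

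**6. Same 2.9 kg mean difference, effect not uniform.**
- Only women above the range shift, control mean 9.05 kg: within 28.6 → 46.1% (SD 5.7, power 54%) or 32.7 → 49.1% (SD 4.9, power 48%).
- The same with control mean 11 kg, SD 5.7: within 25.7 → 52.5% (power 89%).
- Half common shift and half proportional reduction above mid-range, control mean 9.05 kg, SD 5.7: within 28.6 → about 50% (power about 71%). The figure moves by about 2 points with the order in which the two parts are applied.

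**7. The other ranges.** With the Primary Outcome section's ranges, the base case gives within 24.3 → 12.6%. The direction and size of the result therefore depend on which ranges are used.

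**The case against.** A reader might infer that the within-range hypothesis is bound to fail at the plan's own figures. The documents do not support that. The article states no control mean, BMI mix or distribution. The 9.05 kg comes from a ratio in a 31-woman feasibility trial. It is gain during the study, set against bounds for total gain, and it is combined with an SD from a different study that was chosen to be conservative for power.

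Nor is a uniform shift how the intervention is meant to work. The controller steers towards a setpoint at the mean of the guideline range (HMZ 2.0 Pilot Study Results), and adaptation follows a forecast of excess (Adaptive Intervention Dosage Changes). Against that, the baseline dosage goes to all intervention women, and the Figure 4 legend gives the first two step-ups to all of them, so a purely selective effect is not described either. The feasibility trial reported intervention women as more likely to be within goals, where the common-shift model at 1.9 kg gives 0.0 points; but it was small and the article gives no rates. All of this stands, and it makes the flat result a possibility rather than a prediction.

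A reader might also infer that exceeding the upper bound should replace the within-range hypothesis. That is not supported. The stated aim is to regulate gain to a two-sided range. Testing above alone could declare success while the below-range share rises, from 29% to 48% in the base case. Monitoring of insufficient gain under Safety Considerations does not fill this gap: its indicators are weekly and four-weekly, and it sets no between-arm comparison against the lower bound.

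A three-way table could be left to an analysis plan that is not shown. The hypothesis itself is stated here, however, and it names only one of the three shares.

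**Conclusion.** The point holds in conditional form. Within-range is a net share. Under a common 2.9 kg shift from a control mean near 9 kg it changes by about -1 to -2 points with about 5% power, while above falls 18 to 20 points and below rises 19 to 22. With control means of 11 to 15 kg it rises 3 to 11 points. With an effect partly or wholly targeted at high gainers it rises 16 to 21 points or more. The documents do not settle which case applies, so a null within-range result could not be interpreted on its own. The hypothesis is not wrong, but it is insufficient alone. The sample size and the powered outcome, mean gain, are unaffected.

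**What to change.** 1. Keep the within-range hypothesis as stated.
2. Add a companion secondary comparison: the intervention group will be less likely than controls to exceed the upper bound, adjusted for BMI stratum.
3. Compare the share below the lower bound by arm as a safety outcome, and present below, within and above in one table by arm.
4. Before any category is computed, reconcile the ranges in Background and Control Optimization Trial Procedures with those in the Primary Outcome section, and state whether in-study or total gain is compared with the bounds.

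Cost: one more secondary comparison, a table, and a protocol amendment, since recruitment has begun and the article reports 12 women enrolled. No new data are needed.
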